### **3.06 Sampling procedure**

The patients will be enrolled consecutively as they fulfil the eligibility criteria since the number of patients per clinic day (20 to 35) can be evaluated by the study team of one principal investigator and four clinical research assistants.

### **3.07 Randomisation**

Randomisation of the patients to the intervention and control will be performed at individual level using random block sizes of 4, 6, 8, 10, and 12. The randomisation code will be generated by an independent statistician using a computer software called Random Allocation Software version 1.0.0

### **Concealment of the randomisation code**

The codes will be concealed using the sequentially numbered opaque sealed envelopes and kept with the Nurse In-charge who will pick an envelope for each patient that is enrolled in the study using the eligibility criteria.

## **Blinding**

The health workers who will be administering the intervention and the control will not be blinded given that it is not feasible to blind them. However, the research assistant (psychiatric nurse) administering the M.I.N.I., and the patients will be blinded. The research assistant administering the M.I.N.I will not be told which study groups the patients were allocated. The patients too will not be told which arm they have been allocated to.

In addition, the research assistant administering the M.I.N.I will not have access to the presumptive diagnoses from the research assistants administering the PHQ 2 and 9.

### **3.08 Study variables**

#### **The intervention**

The intervention will be comprised of routine screening. In this strategy PLHIV who consent will be subjected to the PHQ-2 and if the patient has a value greater than or equal to 3 in the PHQ-2 the patient will be subjected to PHQ-9. After wards all patients will be subjected to the M.I.N.I to confirm cases of major depressive disorder (MDD), and to identify the missed cases of MDD. The M.I.N.I will be used to identify the actual number of cases of MDD in the group.

#### **The control**

The control arm will provide the standard of care which is selective screening. A patient who consents to the study will be subjected to the PHQ2 and later (if  $PHQ2 \geq 3$ ) PHQ 9 when the clinician finds it appropriate especially at the crisis points in life in accordance with the ministry of health 2016 guidelines for prevention and treatment of HIV in Uganda. The clinician will require to indicate the reason for screening before screening for depression.

After wards all patients will be subjected to the M.I.N.I to confirm cases of major depressive disorder (MDD), and to identify the missed cases of MDD. The M.I.N.I will be used to identify the actual number of cases of MDD in the group.

The crisis points in life include: newly diagnosed with HIV or at disclosure of HIV status; occurrence of any physical illness, recognition of new symptoms / progression of disease or hospitalisation or diagnosis of AIDs; introduction to medication; death of a significant other; necessity of making end of life; and permanency planning decision, major life changes like child birth, pregnancy, loss of a job, and end of a relationship.

### **Outcome variable**

The outcome variable of interest is the percentage of missed cases of depression.

### **The potential confounders**

Basing on literature, the following potential confounders will be considered; age (Payne, 2017) , marital status (Bulloch, Williams, Lavorato, & Patten, 2017), sex (Karger, 2014), weight (Tracy, 2017), viral load (J Peters, 2014).

### **3.09 Data collection**

#### Data collection procedure

The study team will comprise of the principal investigator, two psychiatric nurses, two clinical officers, one social worker and two data entrants

Data will be collected in three consultation rooms. Patients in the intervention arm will be evaluated by a clinician stationed in a consultation room dedicated to the intervention arm. Patients in the control arm will be evaluated by a clinician in a separate room dedicated to the control arm. Finally, all patients will be evaluated by a psychiatric nurse using the MINI in the third consultation room.

#### Measurement of variables

Case detection: These will be measured using the PHQ-2 and the PHQ-9 questionnaires and graded using the guide for diagnosis and management of depression adopted from the Ministry of Health guidelines 2016.

The cases missed by the strategies will be detected using the M.I.N.I. It will therefore be used to determine the denominator (cases of depression present) in both groups.

**The PHQ-2** tool is a two-item instrument that inquires about the frequency of depressed mood and anhedonia over the past two weeks. The purpose of the tool is to screen for depression in a first step approach. The PHQ-2 score ranges between 0–6 and those with a score equal or greater than 3 are further evaluated using the PHQ-9.

**The PHQ-9** is a 9-item depression screening instrument that determines the presence and frequency of the 9 core depressive symptoms identified in the DSM-IV over the previous 2 weeks. This tool has been used in sub-Saharan Africa for a number of studies(Akena et al., 2013). Scores range from 0–27, with a score of 10 or higher usually used to indicate the presence of a depressive disorder that would benefit from treatment. The PHQ-9 was developed to be self-administered, however interviewer-administration and telephone administration (Pence et al., 2012) has yielded similar results.

**MINI**—The Mini International Neuropsychiatric Interview (MINI) is a brief, structured diagnostic interview for major psychiatric disorders. The MINI will serve as the reference standard in this study which will be used to determine the cases in the denominator. The MINI modules for major depressive disorder (MDD) will be used for this study.

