#### Scope of the study

There are several factors that affect screening for depression as shown above (figure 1). All the domains listed above will be studied apart from social support structures and long-term outcomes of management of depression, and the effects of depression management on HIV screening. The outcome variables of interest are cases of depression detected among PLHIV (primary) and the missed cases of depression by the two strategies (secondary).

For the qualitative study the outcome variable is perceptions of stake holders on the screening strategies.

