### 3.11 Data analysis

Skewed data will be summarised using median and quartiles while mean and standard deviation will be used to summarise non-skewed data.

The trial data will be analysed on an intention to treat analysis basis.

Two-Sample Z-Test for proportions will be used to test the single difference between proportions of cases detected in the two study arms (Dawson & G Trapp, 2004) if the data meets the conditions for the statistic otherwise chi square statistics or Fisher's exact test will be used to answer the objective. Missed cases proportions in a group will be calculated as follows,

$$Z = \frac{\hat{p}_1 - \hat{p}_2}{SE} = \frac{\hat{p}_1 - \hat{p}_2}{\sqrt{\hat{p}(1-\hat{p})\left(\frac{1}{n_1} + \frac{1}{n_2}\right)}}$$

$$\hat{P} = (\hat{P}_1 n_1 + \hat{P}_2 n_2) / (n_1 + n_2)$$

Where;

$\hat{P}_1$  is proportion in group one

$\hat{P}_2$  is proportion in group two

$\hat{P}$  is the pooled proportion of  $\hat{p}_1$  and  $\hat{p}_2$

$n_1$  is the sample size of group one

$n_2$  is the sample size of group two.

The estimates' level of significance will be ascertained using the 95% confidence interval and P-value. The estimate will be considered significant if an estimate's confidence interval does not contain the null value and if the p value is less than 0.05.

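### The main outcome is defined in conflicting ways, and the protocol leaves open whether a PHQ-positive, MINI-negative patient counts as a detected case

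*Protocol*

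**What the plan says.** Four parts of the protocol bear on the outcome.

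- **Scope of the study** (Chapter One): "The outcome variables of interest are cases of depression detected among PLHIV (primary) and the missed cases of depression by the two strategies (secondary".
- **3.08, Outcome variable**: "The outcome variable of interest is the percentage of missed cases of depression". Detected cases are not mentioned.
- **3.09, Measurement of variables**: "Case detection: These will be measured using the PHQ-2 and the PHQ-9 questionnaires". The MINI is assigned to the missed cases and to the denominator: "It will therefore be used to determine the denominator (cases of depression present) in both groups". On the PHQ-9 the section speaks of scores "with a score of 10 or higher usually used to indicate the presence of a depressive disorder".
- **3.11 Data analysis**: the Z-test "will be used to test the single difference between proportions of cases detected in the two study arms". The sentence that introduces the formula then speaks of missed-case proportions, and n1 "is the sample size of group one", with n2 defined likewise.

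The MINI is given to everyone. In the intervention arm, "After wards all patients will be subjected to the M.I.N.I to confirm cases of major depressive disorder (MDD), and to identify the missed cases of" that disorder, and the control arm has the same sentence. The Operational Definitions grade PHQ-9 scores of 5-9 as mild depression.

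**The concern.** The trial has one quantitative comparison. Its primary status, numerator, denominator and threshold each have more than one reading. No sentence requires a detected case to be MINI-positive. The cut-off of 10 is reported as common practice and is not set as the trial's rule, while the definitions already use the word depression from a score of 5.

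Two readings are open:

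- **Reading A:** PHQ-positive patients divided by all randomised patients. This follows the detection rule in 3.09 and the group sample sizes in 3.11.
- **Reading B:** PHQ-positive patients among MINI cases, divided by MINI cases. This follows the denominator in 3.09 and the confirming role of the MINI in 3.08.

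Under B, detected and missed are complements and false positives never enter. Under A they are not complements, and every MINI-negative positive counts as a detection. Control patients receive the PHQ only when the clinician sees a reason, whereas every routine-arm patient receives it. False positives therefore accumulate in the arm that screens more non-cases. The same data could give different conclusions under A and B, and the choice could be made after the data are seen.

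**Working it through.** **The protocol's own figure.** Section 3.05 uses p1 = 0.95 and p2 = 0.855, both proportions of cases missed:

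[1.96 × √(2 × 0.95 × 0.05) + 1.282 × √(0.95 × 0.05 + 0.855 × 0.145)]² / 0.095² = (0.6041 + 0.5309)² / 0.009025 = 142.74

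This gives 143 per group, and 172 after adding 20%. The figure reproduces. The proportions refer to cases of depression, but the 172 are patients.

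**Inputs for Reading A.** From 2.02: PHQ-2 sensitivity 82.9% and specificity 90%; PHQ-9 sensitivity 91.6% and specificity 81.2%. Prevalence: 9% is the lower figure for major depression in 1.00, 46% is the upper figure in 1.01, and 20% is an assumed middle value. A patient is positive only if positive on both tests.

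- Independent errors: sensitivity 0.829 × 0.916 = 0.759; false-positive rate 0.10 × 0.188 = 0.0188.
- Full overlap: sensitivity 0.829; false-positive rate 0.10.

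Routine arm: true positives = 172 × prevalence × sensitivity; false positives = 172 × (1 − prevalence) × false-positive rate.

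**Stress test.** Let both arms find the same true cases, so that any excess is false positives only. Control has either no false positives or those from screening half of its non-cases (both assumed). The rejection rate comes from exact enumeration of the two-sided pooled Z-test at 172 per arm.

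| Prevalence | Errors | Routine arm, true / false positives | Positive, routine v control with no false positives | Significant, no control false positives | Significant, control screens half its non-cases |
|---|---|---|---|---|---|
| 9% | independent | 11.8 / 2.9 | 8.5% v 6.8% | 9.1% | 6.0% |
| 9% | full overlap | 12.8 / 15.7 | 16.6% v 7.5% | 75.4% | 22.7% |
| 20% | independent | 26.1 / 2.6 | 16.7% v 15.2% | 6.8% | 5.5% |
| 20% | full overlap | 28.5 / 13.8 | 24.6% v 16.6% | 45.2% | 14.3% |
| 46% | independent | 60.1 / 1.7 | 35.9% v 34.9% | 5.5% | 5.1% |
| 46% | full overlap | 65.6 / 9.3 | 43.5% v 38.1% | 18.0% | 8.2% |

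Independence probably understates the problem. By 2.02 the PHQ-2 items are the first two of the PHQ-9, so anyone referred on already has at least 3 PHQ-9 points. A cut-off of 5 would then need only two more.

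**Inputs for Reading B.** With 8% to 46% prevalence (1.01), MINI cases per arm m = 172 × 0.08 = 13.8 to 172 × 0.46 = 79.1. Power for 0.95 v 0.855, with pooled proportion 0.9025:

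Φ{[0.095 − 1.96 × √(2 × 0.9025 × 0.0975 / m)] / √(0.171475 / m)}

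- m = 13.8: Φ(−1.13) = 13%
- m = 79.1: Φ(0.06) = 52%

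The normal approximation is rough at the low end.

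**The case against.** A reader might infer that detection is measured by the PHQ alone and that routine screening therefore wins by design. The protocol does not support that.

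- The MINI is given to all patients in both arms to confirm cases (3.08). It is the reference standard and the source of the denominator (3.09).
- PHQ results are called presumptive diagnoses under Blinding in 3.07.
- The hypothesis in 1.05, the sample size in 3.05 and the outcome in 3.08 all rest on missed cases, which false positives cannot enter.
- Extra true cases found by screening everyone are the effect under study. Only the false-positive share is bias.

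The largest figures also need an unlikely control arm, one that finds every case the PHQ would find and yet produces no false positive. Section 3.05 assumes instead that selective screening misses 95% of cases.

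All of this stands, and it makes Reading B a fair reading. It does not settle the matter. Section 3.11 tests detected cases and defines its denominators as group sample sizes, Scope of the study makes detected cases primary, and no sentence excludes MINI-negative positives.

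**Conclusion.** The concern holds as a contradiction in the outcome definition that must be resolved before analysis. Scope of the study, 3.08, 3.09 and 3.11 do not agree on the primary outcome or its denominator, and neither the MINI requirement nor the PHQ-9 cut-off is fixed.

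The possible bias exists only under Reading A, and its size runs from trivial to serious. The chance of a significant result with equal true detection is about 5-9% with independent errors, close to the nominal 5%. With full overlap and no control false positives it is about 75%, 45% and 18% at 9%, 20% and 46% prevalence. With half of control non-cases screened, these maxima fall to about 23%, 14% and 8%. The overlap of errors and the share of control non-cases screened are assumptions, because the protocol gives neither. The accuracy figures in 2.02 are taken at face value, and no PHQ-9 cut-off is stated with them.

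**What to change.** Align Scope of the study, 3.08, 3.09 and 3.11 as follows.

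1. Name one primary outcome: the percentage of MINI-positive participants who were not PHQ-positive before the MINI. Control patients who were never screened count as not PHQ-positive.
2. In 3.11, define n1 and n2 as the MINI-positive participants in each arm.
3. Define a detected case as PHQ-positive at one PHQ-9 analysis cut-off, stated in advance, and MINI-positive. Detected and missed are then complements.
4. Report PHQ-positive, MINI-negative counts per arm as a secondary outcome.

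No new data are needed, since every patient already has the MINI. The cost is more than wording. The denominator becomes about 14-79 per arm, so the 90% power implied in 3.05 is not delivered for 0.95 v 0.855 (roughly 13-52%) and should be restated. That restatement should say which contrast it rests on. The PHQ figures in 2.02 imply that full screening would miss about 17-24% of cases (1 − 0.829 to 1 − 0.759), far fewer than the 85.5% assumed in 3.05.

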### **3.10 Data management**

Emphasis will be made on filling questionnaires correctly. The filled questionnaires will be kept securely under lock and key. This will be entered using Epidata by two independent data entrants. The data will be exported to Stata 13 software. The data will be backed up in google drive and an external drive.

### 3.11 Data analysis

Skewed data will be summarised using median and quartiles while mean and standard deviation will be used to summarise non-skewed data.

The trial data will be analysed on an intention to treat analysis basis.

Two-Sample Z-Test for proportions will be used to test the single difference between proportions of cases detected in the two study arms (Dawson & G Trapp, 2004) if the data meets the conditions for the statistic otherwise chi square statistics or Fisher's exact test will be used to answer the objective. Missed cases proportions in a group will be calculated as follows,

$$Z = \frac{\hat{p}_1 - \hat{p}_2}{SE} = \frac{\hat{p}_1 - \hat{p}_2}{\sqrt{\hat{p}(1-\hat{p})\left(\frac{1}{n_1} + \frac{1}{n_2}\right)}}$$

$$\hat{P} = (\hat{P}_1 n_1 + \hat{P}_2 n_2) / (n_1 + n_2)$$

Where;

$\hat{P}_1$  is proportion in group one

$\hat{P}_2$  is proportion in group two

$\hat{P}$  is the pooled proportion of  $\hat{p}_1$  and  $\hat{p}_2$

$n_1$  is the sample size of group one

$n_2$  is the sample size of group two.

The estimates' level of significance will be ascertained using the 95% confidence interval and P-value. The estimate will be considered significant if an estimate's confidence interval does not contain the null value and if the p value is less than 0.05.

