### **3.05 Sample size estimate**

The following formula will be used;  $n = [Z_{\alpha} \sqrt{2p_1(1-p_1)} - Z_{\beta} \sqrt{p_1(1-p_1) + p_2(1-p_2)}]^2 / (p_1 - p_2)^2$ , (Dawson & G Trapp, 2004) where 'n' is sample size per group 'Zα' is the critical value of the Normal distribution at 'α', 'Zβ' is the critical value of the Normal distribution at 'β' and 'p1' and 'p2' are the expected sample proportions of the two groups.

Assuming 95% of the cases of depression are missed in primary care practice by selective screening (Jenkins et al., 2013) and we would like to notice a 10% reduction in the cases missed (Pignone et al., 2002).

$$(P_1 - P_2) / P_1 = 0.1$$

$$P_2 = P_1 - (P_1 * 0.1)$$

$$P_2 = 0.95 - (0.95 * 0.1) = 0.855.$$

$$n = [Z_{\alpha} \sqrt{2p_1(1-p_1)} - Z_{\beta} \sqrt{p_1(1-p_1) + p_2(1-p_2)}]^2 / (p_1 - p_2)^2$$

$$n = [1.96 \sqrt{2 * 0.95(1-0.95)} - (-1.282) \sqrt{0.95(1-0.95) + 0.855(1-0.855)}]^2 / (0.95 - 0.855)^2$$

$n = 142.74 \sim 143$  PLHIV per group and 286 in two groups

Catering for non-response at 20% per group,

$$0.20 * 143 = 28.6 \sim 29.$$

Therefore, a total sample size of 344 patients will be enrolled for the study with 172 PLHIV per group.

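### Section 3.11 puts the whole group's sample size into a Z-test of missed-case proportions whose denominator is MINI-positive cases, so the standard error is too small

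*Protocol*

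**What the plan says.** All references are to the protocol.

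- Section 3.08, Outcome variable: "The outcome variable of interest is the percentage of missed cases of depression".
- Section 3.09, Measurement of variables, on the MINI: "It will therefore be used to determine the denominator (cases of depression present) in both groups".
- Section 3.11 names a two-sample Z-test "to test the single difference between proportions of cases detected in the two study arms". It introduces the formula with "Missed cases proportions in a group will be calculated as follows" and then explains the symbols: n1 "is the sample size of group one", and n2 likewise for group two. The same n1 and n2 weight the pooled proportion.
- Section 3.05 shows what a group's sample size means in this protocol. It arrives at 143 "PLHIV per group and 286 in two groups", raised to 172 per arm for non-response.
- Section 3.11 makes the Z-test conditional: it is used "if the data meets the conditions for the statistic otherwise chi square statistics" or Fisher's exact test. It does not state the conditions. Significance requires a 95% confidence interval that excludes the null value, and also "if the p value is less than 0.05".

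**The concern.** A proportion and the n in its standard error must share a denominator. Here the proportion is missed cases over depressed patients, while the n given for the standard error is everyone in the arm. Unless every participant is depressed, the formula credits the estimate with more information than it has.

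This is the only test given for the trial's quantitative objective. An error in this direction would make routine screening look different from selective screening when the data do not show it. An analyst following the text would find no definition of n other than group size, so entering 172 is a natural reading. Section 3.05 makes the same substitution: it takes 0.95 and 0.855 as proportions of depression cases, then recruits the resulting number as clinic patients.

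**Working it through.** **Inputs.** Missed proportions p1 = 0.95 and p2 = 0.855, Z values 1.96 and 1.282, 20% non-response (section 3.05). Two-sided alpha 0.05 (sections 3.05 and 3.11). Major depression in 9% to 32% of people with HIV in sub-Saharan Africa (section 1.00), and depression in 8% to 46% in Uganda (section 1.01). Prevalence among enrolled patients is not fixed, so values from these ranges are assumptions, and 20% is an illustrative middle value.

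**1. The plan's own figure.** n = [1.96·√(2·0.95·0.05) + 1.282·√(0.95·0.05 + 0.855·0.145)]² / 0.095² = (0.604 + 0.531)² / 0.009025 = 142.74, so 143. Adding 29 gives 172 per arm and 344 in total. The figure reproduces, and it is counted in patients.

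**2. Size of the standard-error fault.** With N patients per arm and prevalence π, an arm holds about m = Nπ cases. The correct SE is √[p(1−p)·2/m] and the literal SE is √[p(1−p)·2/N]. Their ratio is √(N/m) = √(1/π).

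Example at the planned rates: pooled p = (0.95 + 0.855)/2 = 0.9025.
- With n = 172, SE = √(0.9025·0.0975·2/172) = 0.032 and Z = 0.095/0.032 = 2.97.
- At 32% prevalence, m = 55, SE = 0.057 (0.0565 before rounding) and Z = 0.095/0.0565 = 1.68.

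The same observed difference is significant in the first calculation and not in the second.

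**3. Type I error.** The normal approximation is 2·[1 − Φ(1.96·√π)]. The exact values enumerate two independent binomials with m cases per arm (172π rounded down) and a common missed rate, with Z computed using n = 172. The Z-always column covers missed rates 0.76, 0.855 and 0.95. The last two columns use Z with n = 172 only when all pooled expected case counts are at least 5 (an assumed threshold), and Fisher's exact test otherwise.

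| Prevalence | Cases per arm | SE too small by | Approx. | Exact, Z always | Checked on cases, 0.95 | Checked on cases, 0.855 |
|---|---|---|---|---|---|---|
| 9% | 15 | 3.33 | 56% | 55-62% | 0.1% | 1.7% |
| 20% | 34 | 2.24 | 38% | 39-46% | 0.3% | 23% |
| 32% | 55 | 1.77 | 27% | 26-27% | 2.2% | 26% |
| 46% | 79 | 1.47 | 18% | 19-20% | 5.3% | 19% |

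With n set to the number of cases, the Z-always enumeration gives 0.5-5.4%.

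**4. Why the condition check matters.** At a missed rate of 0.95 the expected detected cases per arm are 0.05·m = 0.75, 1.7, 2.75 and 3.95 down the rows. All are below 5, so a check on cases usually sends the analysis to Fisher's test. If the check is also made with 172, the expected counts at the planned rates are 172·0.05 = 8.6 and 172·0.145 = 24.9. Both pass, and Z goes ahead. Repeating the enumeration with the check made on 172 times the pooled proportion gives, at 0.95, about 62%, 35%, 22% and 18% down the rows. Most of the protection is lost.

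**5. Chi-square.** On the same 2×2 table of missed and detected cases, the uncorrected chi-square equals the square of the pooled Z computed with case denominators. It therefore uses the right n, but it depends on the same large-sample conditions and is no remedy when counts are sparse.

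**The case against.** **The wording may only be a generic legend.** The pooled formula in section 3.11 is a true pooled proportion only if n is the denominator of each proportion, and section 3.09 says what that denominator is. A chi-square or Fisher's test on counts of missed and detected cases would also take the right n automatically. This is fair as evidence of intent. But the protocol never defines n as cases, and section 3.05 uses the group size in patients.

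**Another reading has no inflation.** Section 3.11 also speaks of proportions of cases detected, and the Scope of the study section calls cases detected primary and missed cases secondary. If the proportion were cases detected over everyone randomised, group size would be the correct n. That reading conflicts with the denominator in section 3.09, the outcome in section 3.08 and the planned 0.95 and 0.855. The text needs correcting on either reading.

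**Z is conditional, and Fisher's test is listed.** This stands, and it limits the point. A reader might infer that the fallback is empty because chi-square is Z squared. The protocol does not support that, since it also names Fisher's exact test, which is valid on sparse case counts. A reader might equally infer that the trial has a false-positive rate above one half at low prevalence. That holds only if Z is applied regardless of its conditions, or if they are checked with 172.

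**Conclusion.** The concern holds in this form: as defined in section 3.11, the standard error of the missed-case comparison uses the wrong n and is too small by √(1/prevalence), about 1.5 to 3.3 times for prevalence from 46% down to 9%.

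The effect on false positives depends on how the Z conditions are handled. Used unconditionally, Z has a type I error well above 5% at every prevalence examined. Checked on real case counts with Fisher's test as the alternative, the plan is protected at a missed rate of 0.95 but not at 0.855 once prevalence reaches 20%. These results assume the cited prevalence ranges, 172 evaluated patients per arm, equal case numbers in the two arms and a threshold of 5 expected per cell.

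The rule should be corrected before analysis, because it is wrong as written and governs the trial's main comparison. Correcting it does not restore power. At the planned rates, 172 patients per arm give approximate power of 14% at 9% prevalence, 39% at 32% and 52% at 46%. That is a separate matter for section 3.05.

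**What to change.** In section 3.11:

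1. Define n1 and n2, in both the Z statistic and the pooled proportion, as the number of MINI-positive participants in each arm.
2. Define p-hat in each arm as participants who are MINI-positive and not detected by the strategy, divided by all MINI-positive participants.
3. State the Z-test conditions, including the threshold, and check them on those case counts rather than on the number enrolled.
4. Name the already listed Fisher's exact test as the one to use when the conditions fail, and do not rely on the uncorrected chi-square for sparse tables.

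Boschloo's test is optional. With 28 cases per arm and 0.95 versus 0.855 it has about 14% power against 7% for Fisher's, but preferring it corrects no error.

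The cost is a few lines of analysis text. Data collection does not change, since every participant already receives the MINI.
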